## Abstract

**Background:**

Enhancing physical activity in overweight and obese individuals is an important means to promote health in this target population. The Health Action Process Approach (HAPA), which was the theoretical framework of this study, focuses on individual self-regulation variables for successful health behavior change. One key self-regulation variable of this model is action control with its three subfacets awareness of intentions, self-monitoring and regulatory effort. The social context of individuals, however, is usually neglected in common health behavior change theories. In order to integrate social influences into the HAPA, this randomized controlled trial investigated the effectiveness of a dyadic conceptualization of action control for promoting physical activity.

**Methods/Design:**

This protocol describes the design of a single-blind randomized controlled trial, which comprises four experimental groups: a dyadic action control group, an individual action control group and two control groups. Participants of this study are overweight or obese, heterosexual adult couples who intend to increase their physical activity. Blocking as means of a gender-balanced randomization is used to allocate couples to conditions and partners to either being the target person of the intervention or to the partner condition. The ecological momentary intervention takes place in the first 14 days after baseline assessment and is followed by another 14 days diary phase without intervention. Follow-ups are one month and six months later. Subsequent to the six-months follow-up another 14 days diary phase takes place.

The main outcome measures are self-reported and accelerometer-assessed physical activity. Secondary outcome measures are Body Mass Index (BMI), aerobic fitness and habitual physical activity.

**Discussion:**

This is the first study examining a dyadic action control intervention in comparison to an individual action control condition and two control groups applying a single-blind randomized control trial. Challenges with running couples studies as well as advantages and disadvantages of certain design-related decisions are discussed. This RCT was funded by the Swiss National Science Foundation (PP00P1_133632/1) and was registered on 27/04/2012 at http://www.isrctn.com/ISRCTN15705531.

**Electronic supplementary material:**

The online version of this article (doi:10.1186/1471-2458-14-1321) contains supplementary material, which is available to authorized users.

## Background

Regular physical activity has beneficial effects on health [1, 2] just as physical inactivity was identified the fourth leading risk factor for mortality [2]. Current recommendations of the World Health Organization on physical activity for adults are to engage in at least 150 minutes of moderate-intensity aerobic activity or 75 minutes of vigorous-intensity aerobic activity or a combination thereof. The activity can be broken down into several bouts of at least ten minutes duration. Moreover, muscle-strengthening activities on two or more days a week are recommended. There is, however, a discrepancy between these recommendations and the actual physical activity in the adult population worldwide in general [3] as well as in Switzerland in particular [4]. Of the general Swiss adult population 28% do not meet these minimum requirements [4]. Especially for overweight and obese individuals, regular physical activity is highly recommended for weight regulation and health benefits [5]. Prevalence data for overweight or obesity (BMI > = 25) in Switzerland report on 41% in the population older than 15 years [4]. Thus, enhancing physical activity in overweight and obese individuals is of special importance.

Changing one’s unhealthy behavior, however, seems to be a major challenge for most people. This is even the case when individuals report strong intentions to change their behavior: By far not all individuals having a strong intention to change a behavior are successful in doing so, a phenomenon that is known as the intention-behavior gap [6]. There is a plethora of research on health behavior change which is usually based on one of the leading social-cognitive models of health behavior, such as the Theory of Planned Behavior (TPB) [7], the Protection Motivation Theory (PMT) [8], Social Cognitive Theory (SCT) [9], or the Health Action Process Approach (HAPA) [10]. Whereas the TPB, SCT, and PMT assume intentions to be the most important predictor of behavior, the HAPA is one of the few models that explicitly take the intention-behavior gap into account. Studies on physical activity applying the HAPA have demonstrated the model’s utility for this specific health behavior [11–13].

The HAPA distinguishes between a motivational and a volitional phase. In the motivational phase, risk awareness (i.e., the perceived personal health risk due to the unhealthy behavior that needs to be changed), positive and negative outcome expectancies (i.e., perceived advantages and disadvantages of a behavioral change; [14]) and self-efficacy (i.e., the perceived competence to change the behavior despite obstacles; [14]) are assumed to predict intentions. In the volitional phase, in addition to intentions and self-efficacy, volitional predictors are specified to explain behavior. These are action planning (i.e., when, where, and how to implement the intended behavior; [15–17]), coping planning (i.e., anticipating barriers to the intended behavioral change and planning how to overcome these barriers; [18]) and action control. Action control is based on the concept of feedback loops from the self-regulation theory by Carver and Scheier [19] and comprises three subcomponents: awareness of standards, self-monitoring, and self-regulatory effort [20]. Awareness of standards is comparable to the standard value in feedback loops, but refers not only to setting an intention but also to remembering this intention in situations important for the respective self-regulatory action. Without being aware of one’s own standards/behavioral intentions, successful self-regulation cannot be accomplished. Self-monitoring refers to the attentive monitoring of qualitative and quantitative aspects of one’s own behavior. Research on self-monitoring has identified this component to be of great importance for successful self-regulation e.g., [21, 22]. In the concept of action control, self-monitoring is also assumed to trigger the comparison between the intended and the actual behavior [23]. If a discrepancy between a person’s standard (e.g., behavioral intention to eat five portions of fruits and vegetables a day) and his/her actual behavior (e.g., having eaten only two portions of fruits and vegetables today) is detected, action must be taken. This is the function of the third component, self-regulatory effort: Appropriate means of reducing the discrepancy between actual and intended behavior must be applied [20]. Action control has been demonstrated to be effective in translating intentions into behavior in both correlational [20, 24] and experimental studies [23, 25].

There are several experimental means to foster action control. Two behavior change techniques are directly related to action control: “self-monitoring of behavior” and “discrepancy between current behavior and goal” [26]. Moreover, one approach that has, however, not yet been linked explicitly to action control is the use of reminders, as these address not only the awareness of intentions, but are also assumed to stimulate self-monitoring and (indirectly) self-regulatory effort. Research on the effects of reminders is very common in the context of adherence e.g., [27, 28]. Studies on reminder systems – either with technology support like online-pagers or simple telephone or mail reminders - provide good evidence that this is a useful tool to promote the implementation of an intended behavior. Likewise, there are some studies on mobile phone based text message reminders demonstrating the effectiveness of these interventions [29].

### Dyadic approaches to health behavior change models

Individuals usually try to change their health behavior (or refrain from doing so) while being embedded in a social network of partnership, family, friends and colleagues. Almost no health behavior change theory, however, takes the social context explicitly into account^a^. Instead the focus usually is on individual self-regulation. One approach to include social exchange processes into health behavior change models is to add the most prominent ones, social support and social control, as predictors [31–33]. A recent alternative attempt to introduce a social component into health-behavior change research is the dyadic conceptualization of originally individual components of health behavior change models that have been shown to be of importance for successful behavioral change on the individual level. One such approach is the concept of collaborative/dyadic planning with a partner [34–36]. For example, Prestwich and colleagues [35] investigated the effect of collaborative action planning on physical activity, when plans were formed *and* enacted together with a partner. The authors found that all participants who planned collaboratively were more successful in increasing their physical activity than individual planning or control group participants. Moreover, Burkert and colleagues [34] found that action control and social control mediated the effects of a dyadic planning intervention. What has not yet been targeted on the dyadic level, however, is action control. This was the main aim of the present study. Targeting dyadic action control can be done by focusing on the partner as the provider of text messages addressing the behavior-specific components of action control (self-monitoring, awareness of intentions, self-regulatory effort) for the target person. Applying an experimental manipulation of dyadic action control provides a strong test for dyadic influences in behavior change. Moreover, it can also considerably further our knowledge on the role of social exchange processes within a health-behavior change framework as enhanced levels of social control and social support are the assumed main mediating mechanisms of a dyadic action control intervention. Furthermore, interactions between individual self-regulation abilities and experimental conditions can be examined in order to further test the hypothesis that social regulation might compensate for deficits in individual regulation capacities on an experimental basis. To the best of our knowledge, this has not yet been done.

### Intra- and interpersonal level of analysis

Although all theories of health behavior change postulate time-dependent processes occurring within individuals, the vast majority of studies analyze the data on the between-subjects level. Associations at the within (intrapersonal) or between (interpersonal) level, however, can differ substantially [37]. As a consequence, a stringent test of our theories will always require testing the theory on both levels of analysis. A related criticism on standard RCTs is that the level of (longitudinal) assessment is usually on a macro-time-level (e.g., baseline and several weeks or months follow-up), which usually only allows interpersonal analyses, but not on a micro-time level (i.e., daily or weekly assessments) cf. [38] which would allow testing for intrapersonal associations. This means that, for example, a randomized controlled trial with baseline assessment, treatment and a follow-up assessment can answer questions on treatment effects (e.g., on physical activity) and on mediating processes at the between-person level (e.g., whether the treatment effect is achieved by increased self-efficacy induced by the treatment). It is not possible, however to answer questions on processes that take place in the time right after the intervention and within persons (e.g., the development of self-efficacy in relation to mastery experience on a daily or weekly basis; [39]).

This can be addressed by applying micro-time assessments. Micro-time assessment comprises weekly or daily diary data e.g., [40] or ambulatory momentary assessment (AMA) e.g., [41]. Studies are needed that combine assessments on macro-time and micro-time levels. For example, randomized controlled trial designs that aim at changing behavior on a macro-time level (i.e., six or twelve months after treatment) can be combined with micro-time assessments in the first phase after treatment. Another alternative is to apply an ecological momentary intervention (EMI), that is, “…treatments characterized by the delivery of interventions to people as they go about their daily lives” [42] in combination with momentary assessment and longer-time follow-ups. This allows capturing comprehensively the processes taking place during as well as (right) after dyadic and individual interventions during everyday life [42].

### Aims of the present study

The aims of the present study are fourfold. The first aim is to examine the effectiveness of a dyadic action control intervention in comparison to an individual action control condition and two control groups. Second, we aim at examining whether a dyadic action control intervention is especially beneficial for individuals low in their individual self-regulation capabilities. Third, mediating mechanisms of the dyadic and individual action control conditions will be examined and compared. The proposed design will allow examining micro- and macro-time changes in outcomes as well as potential mediating mechanism using a daily diary assessment together with objective assessment of the target behavior. Fourth, potential gender differences will be examined. For the hypotheses related to these aims, please see the trial registration: http://www.isrctn.com/ISRCTN15705531. This trial was registered on 27/04/2012.

## Methods/design

Participants of this trial are heterosexual couples, who live in a committed relationship for at least 12 months and cohabit for at least 6 months. Both partners have to be overweight or obese (BMI ≥ 25) and both need to be physically inactive and have the intention to change their physical activity patterns. These requirements are made because an action control intervention is assumed to be only beneficial in a postintentional sample [10]. Moreover, both partners should speak German fluently, be between 18 and 75 years old, and have the possibility to receive and read text messages throughout the day. Women should not be pregnant and both partners should not work in 24 h shift work and should not participate in a professional weight loss program.

This single-blind randomized controlled trial comprises a longitudinal design with micro- and macro-time assessments. Recruitment is organized via advertisements in newspaper and on webpages, flyer and postings in medical and sport facilities, public transport, local companies and mailings to private households in the city of Berne and surroundings, and a marketing research institution. Interested people can send an email to the study team or use a contact page on the homepage of the University of Berne. Participants are then contacted via telephone and inclusion and exclusion criteria are checked. In case of couples meeting all inclusion criteria, both partners are sent separate links for a short online-questionnaire (T0) for which participants provide informed consent. After both partners have completed the online questionnaire, participants are contacted again and are invited to the lab. If participants report having at least one health concern with regard to engaging in physical activity in the short online questionnaire, they are asked to contact a doctor prior to study participation and to check with the doctor whether or not participation for them is possible. At the baseline assessment (T1) participants receive full information on the study, provide informed consent and complete the baseline questionnaire and objective assessments. Moreover, the first part of the intervention for all but the control groups is implemented and they are introduced to the technical devices for the study (smartphones and accelerometers). The day after baseline, a 28 days diary and accelerometer phase starts (D1_1-D1_28). These 28 days comprise during the first 14 days the main part of the intervention for all but the control groups. One month after baseline the first follow-up (T2) takes place. Participants are again invited to come to the lab to return the smartphones and accelerometers and to complete another questionnaire and objective assessments. Six months later, the second follow-up takes place (T3), including again the completion of a questionnaire and objective assessments in the lab. Subsequently, a second 14 days smartphone-based diary and accelerometer phase takes place (D2_1 – D2_14) (see Figure 1 for the longitudinal design). All participating couples receive 200 Swiss Franks as a financial incentive for completing the study.

**Figure 1 Fig1:**
[figure not shown]
**Longitudinal design.**

### Randomization

The randomization comprises on the one hand the randomization to one of the four groups (two control groups and two intervention groups) and on the other hand the gender-balanced randomization of the couple into a target person receiving the intervention and a partner condition. For this reason, blocking as means of restricted randomization is used. Within a block of eight participating couples, two couples each are assigned to one of the four groups, once the man and once the woman assigned as target person. Before the beginning of the study, a computerized random-number generator is used for sequence generation of blocks. This allocation sequence is generated by an assistant that is not part of the study team and concealed in a set of sealed, numbered envelopes, and thus remain unknown to any of the investigators until the group assignment. On the day of the baseline assessement (T1), the interviewer conducting the session opens the appropriate numbered envelope and prepares the study materials accordingly.

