#### Experimental group I: dyadic action control group

After completing the assessments at the baseline session, target persons and their partners are instructed to collaborately form behavioral intentions to increase the target person’s physical activity to the recommended levels (e.g., “get off the bus two stops earlier when going to work” or “take the bike instead of the car”). This is supervised by a trained interviewer in order to ensure the correctness of the behavioral intentions. In terms of BCTs this part of the intervention comprise goal setting (behavior) [26].

Partners are instructed to send daily standardized text messages aiming at increasing the target person’s physical activity-specific action control in personalized form (e.g., “Dear Peter, which of the planned activities have you already carried out today? Love, Regula”) on weekdays during the two weeks following baseline assessment. All action control messages were developed by the authors and reviewed with regard to their action control content by two external reviewers who are experts in the field. A full list of all ten messages can be found in the Additional file 1: Table S1. In terms of BCTs, the different messages target self-monitoring of behavior and discrepancy between current behavior and goal [26]. Moreover, some messages are simple reminders on the behavioral intentions, targeting the awareness of own standards. Partners are instructed to save the personalized text messages as drafts in their study smartphones at the baseline assessment under the supervision of the study interviewer, and receive a reminder text message from the study personnel every day instructing them to send the text message within an hour (and to fill in the diary at the end of the day). Target persons are not informed about the instructions given to the partner, and both partners are asked not to talk about the text messages during the ongoing diary phase.

Moreover, both target persons and partners are instructed not to delete any of these SMS from the smartphones as this will allow a control of the implementation of the study protocol by participants [43].

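### A fixed block of eight, with each group-by-target-sex cell used once, leaves concealment not assured for up to one group assignment in seven

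*Protocol article*

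**What the plan says.** The Randomization section of the protocol article sets one block size and fixes its contents. It states: "Within a block of eight participating couples, two couples each are assigned to one of the four groups", and adds "once the man and once the woman assigned as target person". No other block size and no variation in size is described.

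On concealment, the section says: "This allocation sequence is generated by an assistant that is not part of the study team". The sequence is "concealed in a set of sealed, numbered envelopes, and thus remain unknown to any of the investigators until the group assignment". On the day of baseline (T1), "the interviewer conducting the session opens the appropriate numbered envelope and prepares the study materials accordingly".

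The interviewer's knowledge of the group does not end there. For the dyadic group, the article says of the joint forming of intentions: "This is supervised by a trained interviewer in order to ensure the correctness of the behavioral intentions". The individual action control group has a parallel step. The two control groups form no intentions. The Methods/design section calls the trial single-blind ("This single-blind randomized controlled trial comprises a longitudinal design with micro- and macro-time assessments") but does not say there who is blinded.

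**The concern.** Sealed envelopes and an outside generator hide the list. They do not hide the end of a block of known, constant size from a person who has seen the earlier allocations in it. When seven of the eight cells have been used, the eighth is fixed. The article nevertheless says without qualification that the sequence stays unknown to the investigators until assignment.

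Selection bias is what is at stake. Before the envelope is opened there is a telephone eligibility check, an online questionnaire, a second contact and an invitation to the laboratory. The envelopes are numbered and opened on the day of T1, so if they are used in order, the order of T1 sessions decides which couple gets which allocation. Full study information and the second informed consent also come at T1. Foreknowledge of the next group could affect the order in which couples are invited, or how the study is explained to them. With 29 couples planned per group, a few such couples would be noticeable.

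**Working it through.** **Inputs**
- Block of 8 couples, 4 groups, 2 couples per group, one per target sex (Randomization).
- 116 couples planned, 29 per group (Power analysis).
- Assumptions not stated in the article: the observer knows the block rule and all earlier allocations in the current block. The other extreme is an observer who knows neither, for whom nothing is predictable.

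**Reproducing the block.** 4 groups × 2 target sexes = 8 cells, each used once. This matches the stated block of eight with two couples per group.

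**Group known with certainty, all earlier couples allocated**
- Position 8: always known.
- Position 7: known only if the last two couples belong to the same group. Given the last couple's group, 1 of the other 7 places holds its companion, so the probability is 1/7.
- Position 6 and earlier: at least three couples remain and no group has more than two, so the group is never known.
- Expected number per block: 1 + 1/7 = 8/7. Share: (8/7)/8 = 1/7 = 14.3%.

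Enumeration of all 8! = 40,320 orderings gives the same 8/7 per block.

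**Full allocation (group and target person) known with certainty.** Only position 8: 1/8 = 12.5%.

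**Numbers of couples.** 116/8 = 14.5 blocks. The final half block covers only positions 1 to 4 and adds nothing.
- Group: 14 × 8/7 = 16 expected couples (16/116 = 13.8%).
- Full allocation: 14 × 1 = 14 couples (14/116 = 12.1%).

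**Best guess.** Always naming a group with the most places left is right for 47.0% of couples in the enumeration, against 25% under simple randomization to four groups.

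**Sensitivity to pending couples.** Scheduling happens before the envelope is opened, so earlier couples in the sequence may still be unallocated.

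| Earlier couples still unallocated | Group certain | Best guess correct |
|---|---|---|
| 0 | 14.3% | 47% |
| 1 | (1/8)(1/7) = 1.8% | 38% |
| 2 | 0% | 34% |

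With one pending, certainty needs the couple to be eighth and the last two places to belong to the same group. With two pending, at least three places are open and no group can fill them all. The best-guess figures in the last two rows come from simulation. The article does not say how many couples are usually pending.

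**Mixed blocks of 8 and 16, equally likely, with the observer knowing the possible sizes and where blocks start**
- In a block of 16 each group has four places. Expected certain positions at its end: 1 + 3/15 + (3/15)(2/14) + (3/15)(2/14)(1/13) = 1.23.
- In a block of 8 nothing is certain, because a block of 16 remains possible.
- Share: 1.23/(8 + 16) = 5.1%. Simulation agrees, with a best guess of about 44%.
- For comparison, a known fixed block of 16 gives 1.23/16 = 7.7%.

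**The case against.** The strongest reply is that the weakness is conditional. The article describes generation outside the study team and sealed, numbered envelopes opened on the day. Even in the worst case, six in seven group assignments stay uncertain. It says only that the interviewer conducting the session opens the envelope. It does not say how many interviewers there were, whether they pooled earlier allocations, or whether they were told the block rule. The description of telephone screening and invitation names no actor. The block also has a stated purpose, namely gender balance across the four groups.

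All of this stands, and it limits the point. A reader might infer that the described concealment failed, or that couples were steered because the same people screened, scheduled and interviewed. The documents support neither inference. They show an opportunity whose size depends on unstated facts, and the 14.3% and 47% are its upper bounds. A reader might also treat one in seven as the rate for the whole allocation, but it is the rate for the group only.

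The reply does not remove the point. The block rule is the investigators' own description, and the concealment sentence refers to any of them. Allocations are visible inside the team: interviewers deliver the group-specific steps, and study personnel send messages whose content differs by group and by role. Nor is this a detail left to a fuller document, because the article states both the fixed block and the unqualified claim.

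**Conclusion.** The point holds as a conditional weakness of low severity that is cheap to improve. A fixed block of eight with each cell used once does not guarantee that allocations stay unknown until assignment. If staff know the rule and track earlier allocations, up to 1 in 7 group assignments and up to 1 in 8 full allocations are predictable before the envelope is opened. These bounds assume complete knowledge and no pending earlier couple, and one pending couple is enough to bring the group figure down to about 1.8%. The concealment statement is therefore not assured for those couples, which is different from having been shown false. Bias would further require that a person with this knowledge could influence screening, invitation or order, and the article is silent on that.

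**What to change.** For any couples not yet allocated, have the independent assistant generate the remaining sequence in randomly mixed blocks of 8 and 16, with each group-by-target-sex cell used once or twice. Keep the sizes from interviewers and recruiters until allocation ends. Balance of groups and of target sex is preserved in every completed block.

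The gain is mainly in certainty, from 14.3% to about 5% of group assignments. The best guess moves only from 47% to about 44%, even though the sizes are mixed. The reason is that seven different cells in a row point strongly to a block of eight. In a block of 16 that run has probability (16·14·12·10·8·6·4)/(16·15·14·13·12·11·10) = 0.09, so with equal mixing the block is one of eight with probability 1/(1 + 0.09) = 92%. These figures assume that the possible sizes and the block starts are known, which is why non-disclosure is part of the change.

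The cost is regenerating the unused envelopes, plus a slightly larger possible imbalance if recruitment stops inside a block of 16. The article's discussion refers to recruitment in the past tense, so few or no envelopes may remain. If allocation is complete, qualify the concealment sentence and report who knew the block rule and who scheduled the T1 sessions.
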